#### Setting

Multi-centre recruitments will take place in Australia via established cohort studies at the University of Tasmania and the University of Sydney, aiming for 500 adults aged 50 years old or more. Participants will be assessed online at home (or their own preferred remote setting) or in the University clinical research facilities if they prefer. It is expected that most will complete the tests at home. They will use a laptop computer or desktop computer with a webcam and microphone. Participants who have not already provided a blood sample for their respective studies, will be invited to attend the University clinical research facilities to do so.

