#### Measurements

Each participant will complete TAS Test online at baseline with follow-ups 3 and 6 months later. They will also be invited to provide a blood sample at baseline for p-tau181 levels. The plasma p-tau181 levels will be measured using the ultrasensitive Single Molecule Array immunoanalyser (Simoa®, Quanterix) at the University of Tasmania. Previous research established p-tau181 > 1.81 pg/ml as sensitive and specific to preclinical AD, and highly predictive of AD risk (hazard ratio 10.9) in people with unimpaired cognition or MCI [9]. However, in recognition that the research field of blood-based biomarkers is rapidly evolving [34], and the threshold levels will depend on the assay used, we will use a cut-off value determined through an examination of the most current literature.

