#### Design

We will undertake a prospective 5-year cohort study. We will invite 10,000 adults from a long-term cohort to complete online tests at home: (i) TAS Test every 12 months, and (ii) Cambridge Neuropsychological Test Automated Battery (CANTAB) [42] cognitive tests every 24 months. The prospective ‘high risk’ predictions of TAS Test will be validated against CANTAB, and clinically via in-person testing in a subsample of 300.

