### Sample size

#### Aim 1

We estimate that 17% (or 85 individuals) in the cognitively unimpaired THBP & HBA cohorts will have p-tau181 in the preclinical AD range [45]. We have performed ROC curve analysis using open data from Mollica et al. [19]. This showed area under ROC curve (AUC) of 0.75 for a null linear model including age, sex, ApoE4, and years of education, but not finger tapping, to detect p-tau181 positivity in CSF. To develop the multivariable model, power calculation showed the sample size to compare a screening test with an area under the curve (AUC) > 0.90 against the null model would require 60 positive p-tau181 cases and 290 controls. Thus, we will use 350 in the development dataset (expected 60 [17%] preclinical AD cases) and 150 in the validation dataset (expected 25 [17%] preclinical AD cases) to test cut-offs from the development model. The PROBAST tool [46] confirmed these combined development and validation strategies lower the risk of bias.

#### Aim 2

Based on the age distribution of ISLAND participants, we project that 8.6% of participants currently aged 70–74 years (a cohort of ~ 1300 from the 10,000 recruited) will develop dementia, and more than 16% of the 700 participants currently aged 75+ years will develop dementia over the study duration [47, 48]. Thus at least 200 participants will meet diagnostic criteria for dementia or MCI. Our sample size calculation aims to ensure precise estimation of model parameters while minimising potential of overfitting. A sample of 300 including 100 dementia cases would ensure accurate prediction of the outcome proportion (33%) with a targeted confidence interval of 28–38%. To target a mean absolute prediction error (MAPE) < 0.05, as recommended by Riley et al. [49], a sample of 300 would be adequate for up to 6 predictors in a parsimonious, statistically determined risk prediction model.

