To validate prospectively against cognitive decline, we will assess the sensitivity and specificity of TAS Test to predict cognitive trajectories (“stable” and “declining”) using ROC curve analysis. We will estimate 5-year cognitive decline/MCI/AD risk using baseline TAS Test data in a sub-sample of 300 people. Clinical diagnostic categories are: cognitively unimpaired, MCI, and AD. Covariates considered in the model will include age, sex, ApoE4, years of education, and handedness. We will use Bayesian multinomial logistic regression with regularizing priors to estimate the covariate adjusted log-odds of being in each diagnostic category at 5 years as predicted by baseline TAS Test results. The resulting prediction model will estimate posterior highest density intervals for 5-year risk of conversion to MCI and AD using TAS Test results. There is a risk that not all participants classified as MCI will have prodromal AD (as MCI is a heterogeneous group with a variety of causes) but to account for this, we will perform post-hoc analyses of sub-groups with indicators of higher risk, for example, amnestic sub-type of MCI, p-tau181 positive, ApoE4, longitudinal cognitive decline. Data analysis and statistics will be performed in consultation with a biostatistician.

*Descriptive statistics*: The quantitative variables will be described using mean, standard deviation (SD) and range, or median and inter-quartile range if not normally distributed; Qualitative variables will be described using frequency and percentages.

*Test-retest reliability* will be assessed between the first and second completions of TAS Test at home (12 months), and between completions in the research centre and the home (3–6 months). Stability of the TAS Test assessments will be analysed by measuring the intra-class correlation coefficient and by use of Cohen’s kappa coefficient of agreement.

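### Neither planned test-retest comparison isolates measurement error, and the same-setting 3-month repeats already scheduled in Aim 1 are not named for reliability

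*Protocol article*

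**What the plan says.** The reliability plan is a short paragraph at the end of Statistical analysis in the Protocol article. It names two comparisons, saying that reliability of this kind "will be assessed between the first and second completions of TAS Test at home (12 months), and between completions in the research centre". Taken one at a time, they are:

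- Home to home, at an interval of 12 months.
- Research centre to home: "and between completions in the research centre and the home (3–6 months").

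The statistics are named but the ICC form is not: "Stability of the TAS Test assessments will be analysed by measuring the intra-class correlation coefficient and by use of Cohen’s kappa coefficient of agreement".

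Three other sections bear on which data exist.

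- Aim 1, Measurements: "Each participant will complete TAS Test online at baseline with follow-ups 3 and 6 months later".
- Aim 1, Setting: participants test at home or, if they prefer, in university facilities. "It is expected that most will complete the tests at home".
- Aim 2, Design: "TAS Test every 12 months", online and at home.

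**The concern.** A retest estimate is meant to show how much a score varies when the person has not changed. That calls for an interval short enough for the trait to be stable, and for the same conditions on both occasions. Each planned comparison meets one of these requirements and misses the other.

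The 12-month pair keeps the setting fixed but leaves a year for people to diverge. The 3–6 month pair is shorter, but one completion is at the research centre and the other at home. A difference there may come from elapsed time, practice, or place (including a different computer).

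At stake is how the instrument's noise is described. TAS Test is new, is to be repeated every year, and is proposed for population screening. A reader of annual scores needs to know how large a difference can arise with no change in the person. Neither planned figure answers that cleanly.

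**Working it through.** The documents give no reliability target, expected ICC or sample size for this analysis, so there is no figure to reproduce. The check has three steps.

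**1. Match each comparison to a schedule.** Twelve months fits the annual testing of Aim 2. Three to six months fits the Aim 1 repeats. An Aim 1 participant who tests at home makes the first and second home completions 3 months apart, so the 12-month label does not fit that cohort. The paragraph does not say which cohort supplies which pair. The one combination it does not name is same setting at under 12 months, which Aim 1 is expected to yield for most participants at months 0, 3 and 6.

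**2. Is true change over 12 months plausible on the plan's own terms?** Aim 2 excludes probable or known dementia and some neurological disorders, but does not list mild cognitive impairment as an exclusion. In Sample size, Aim 2, "we project that 8.6% of participants currently aged 70–74 years" will develop dementia, and more than 16% of those aged 75 or over. Spread evenly over 5 years (an assumption), the annual rates are:

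- age 70–74: 1 − (1 − 0.086)^(1/5) = 0.018
- age 75+: 1 − (1 − 0.16)^(1/5) = 0.034, as a minimum

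Some individual change within a year is therefore expected. The Background also argues that movement deteriorates across the disease course.

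**3. How far could the ICC move?** Take two occasions, X1 = T + e1 and X2 = T + m + D + e2, with var(T) = r0 and var(e) = 1 − r0. Here r0 is the short-interval, same-setting reliability, d is the SD of individual change D (independent of T), and m is the mean shift. Both d and m are in baseline SD units. Then:

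- consistency ICC = 2·r0 / (2 + d²)
- absolute-agreement ICC = 2·r0 / (2 + d² + m²)

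All three inputs are assumptions: r0 from 0.70 to 0.90, d and m from 0 to 0.4.

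| r0 | d | m | Consistency | Absolute agreement |
|---|---|---|---|---|
| 0.80 | 0 | 0 | 0.800 | 0.800 |
| 0.80 | 0.2 | 0.2 | 0.784 | 0.769 |
| 0.80 | 0 | 0.4 | 0.800 | 0.741 |
| 0.80 | 0.4 | 0.4 | 0.741 | 0.690 |
| 0.70 | 0.4 | 0.4 | 0.648 | 0.603 |
| 0.90 | 0.4 | 0.4 | 0.833 | 0.776 |

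For example, with r0 = 0.90 and d = m = 0.4, absolute agreement is 1.80 / 2.32 = 0.776, a fall of 0.124. That is the largest fall in the range; the smallest is 0. The third row shows that a shift common to everyone leaves the consistency ICC untouched. Individual differences in change lower both forms.

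**The case against.** The strongest reply is that both comparisons answer useful questions. Twelve months is the interval at which Aim 2 will use the test, so agreement over a year is worth knowing, and the paragraph itself uses the word stability. Centre-home agreement matters because both settings are allowed. Real change over a year may also be small. The dementia projections cover about 1,300 + 700 = 2,000 of 10,000 people, and the annual rates above give roughly 1,300 × 0.018 + 700 × 0.034 ≈ 47 new cases a year. At d = m = 0.2 the ICC falls only from 0.80 to 0.784 or 0.769. All of this stands. It is a reason to keep both comparisons, but it does not turn either into an estimate of measurement error.

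A reader might infer several stronger points that the documents do not support.

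- *That decline over a year, practice and place all enter one comparison.* There are two: the 12-month pair stays at home, and the setting-change pair does not span a year.
- *That the 3-month repeats go unused.* The 3–6 month window matches the Aim 1 schedule, so these repeats appear to enter through the centre-home pair. What is not named is their same-setting use.
- *That every practice or place effect is scored as error.* A uniform shift counts only in an absolute-agreement ICC. The form is not stated, and an article may fairly leave it to the analysis plan.
- *That items sensitive to early disease would be discarded for low reliability.* No section uses the ICC or kappa to keep or drop items. Models are developed against p-tau181, with cross-validation for model selection.

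**Conclusion.** The point holds as a limited one. The two named comparisons do not isolate measurement error: the first admits individual true change over a year, and the second confounds time and practice with setting. Better-suited data are already scheduled in Aim 1 and are not named for this use.

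The direction for individual change is clear, because it lowers the ICC in either form. The size is not known from the documents. The range of 0 to about 0.12 rests on assumed values of reliability, change and shift, and on change being independent of the true score. It does not support a prediction that a reliable test would be reported as only moderately reliable.

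This is a secondary analysis. It does not drive the sensitivity, specificity or ROC results of Aim 1 or the risk estimates of Aim 2. The change is worth making because it replaces a stated, weaker comparison with a cleaner one from data already planned.

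**What to change.** Change the reliability paragraph as follows.

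- **Test-retest reliability:** the home-home ICC in Aim 1 from baseline to month 3, with month 3 to month 6 as a second pair, after first exposure to the test. Report the mean shift in each pair as the practice effect. State the ICC form.
- **Longitudinal stability:** keep the 12-month home-home ICC under this name, and say that it comes from the annual Aim 2 testing.
- **Setting agreement:** report centre-home separately, beside home-home pairs at the same interval, so that the setting effect can be read against the effect of time and practice alone.
- **Source:** say which cohort supplies each pair, which also resolves the 12-month label for first and second home completions.

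The 3-month pair may still contain some practice and change, and it describes cognitively unimpaired people; the report should say so. No visit, test or participant is added. The cost is revised wording and a little extra analysis.

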### Data management

All data will be collected online from the participants and stored in databases hosted on the University of Tasmania virtual server farm managed by central IT and backed up daily. Server access is restricted to authorised administrators using Secure Shell and Public Key Infrastructure certificates. Direct access to the databases is limited to system administrators and overseen by designated custodians of the data and will enable access to data in a de-identified fashion to research personnel. Data will be maintained in secure University of Tasmania databases for at least 10 years, and/or until 5 years after the final publication relating to this data, and consent will be sought for this long-term storage as well as linkage to extension projects. We will also be requesting that consent is provided to enable sharing of non-identifiable data with research collaborators external to the University of Tasmania. The study sponsor organisation is the University of Tasmania, Hobart, Australia, 7001. The study management group comprising clinicians, neuroscientists, computer scientists, and a statistician, will meet every month to monitor and discuss the progress of the study, and to address any issues that may arise. Protocol deviations will be reported to the Human Research Ethics Committee in line with local recommendations.

## Discussion

The planned outcome of this project is TAS Test, a new inexpensive computer screening test to estimate the risk of preclinical AD, cognitive decline and AD dementia. If validated, this new scalable tool can potentially transform dementia prevention and research globally. The significant advantages of using a hand-movement based protocol, along with a broad measure of oromotor, visuospatial, memory and language functions, are sensitivity to early preclinical AD and a protocol that has minimal language or cultural barriers. The advantages of using an online test with standard computer equipment is the global reach of the internet crossing geographical barriers and providing accessibility for people in rural and remote communities and those in low-income countries.

Potential risks of the study are acknowledged and strategies to mitigate these are now discussed. There is a risk of inadequate recruitment but we will mitigate this by recruiting existing participants in established research cohorts, namely the longitudinal cohorts of THBP, HBA and ISLAND. There is a risk that TAS Test is not sufficiently accurate but we have mitigated this risk by selecting component test items based on evidence of sensitivity to preclinical AD, combining multiple tests to amplify the multivariable model input data [> 10,000 data points], and electing well-established, transparent statistical modelling approaches that reveal the most discriminatory components of motor-cognitive data, allowing further refinement. We have also devised a study protocol that plans to collect a sufficiently large dataset to employ multiple modelling methods, including feature-agnostic deep learning. A further risk is that participants lack a computer camera to provide video-recorded hand movement data, or do not wish to do so; we have mitigated this risk by recruiting participants from studies that have online assessments already, offering the opportunity for participants to attend the clinical research centre in person if preferred, and providing alternate methods (such as keyboard tapping test and mouse click reaction time tests) within TAS Test that collect movement data. It is conceivable that some participants will not want to know their dementia risk and this will hinder selection of participants for the clinical subset assessments, but we have minimised this risk by recruiting from studies that focus on reducing dementia risk, where participants have already undergone multiple tests of dementia risk. It is also important to acknowledge that, as the bulk of this project relies on self-report of known neurological diagnoses, we have limited ability to make distinctions between other neurodegenerative disorders, including other forms of dementia and disorders which are correlated with dementia (for example, Parkinson’s disease). Finally, there are risks around COVID-19 pandemic restrictions limiting recruitment or progress of the study; as most of the study is based around online movement and cognitive tests that can be completed at home, there are likely to be minimal effects and we will be able to collect blood for p-tau181 levels using personal protective equipment or at a later date.

In summary, this study directly addresses the critical need for population-level screening tests to detect the earliest stages of dementia. ‘*We can’t manage what we can’t measure’* sums up a global critical struggle against the rising tide of dementia and the odds are stacked against drug trials and preventative strategies as AD is typically detected so late in the disease course - when cognitive symptoms arise. Without a screening test to identify preclinical AD risk *early*, our preventive strategies will remain blunted and belated. There is high potential that TAS Test may provide a scalable screening approach, where the test equipment is already in our homes and health centres.

## Data Availability

The datasets used and/or analysed during the current study are available from the corresponding author on reasonable request.

## Abbreviations

AD: Alzheimer’s disease
AI: Artificial intelligence
Aβ: Amyloid beta
BRAIN: The BRadykinesia Akinesia INcoordination Tap Test
CANTAB: Cambridge Neuropsychological Test Battery
COVID-19: Coronavirus disease 2019
CSF: Cerebrospinal fluid
FT: Finger tapping
HBA: Healthy Brain Ageing Program
ICT: Information and Communication Technology
IPV4: Internet Protocol Version 4
ISLAND: Island Study Linking Ageing and Neurodegenerative Disease
MAPE: mean absolute prediction error
MCI: Mild Cognitive Impairment
MRI: magnetic resonance imaging
ms: milliseconds
NHMRC: National Health and Medical Research Council
PAL: Paired Associate Learning
PD: Parkinson’s disease
PET: Positron emission tomography
pg/ml: picograms per millilitre
P-tau: phosphorylated tau
ROC: Receiver Operating Characteristic
SD: standard deviation
SIMOA: Single Molecule Array immunoanalyser
TAS Test: Tasmania Test
THBP: Tasmanian Healthy Brain Project
USD: United States Dollars
UTAS: University of Tasmania
